### Statistical Analysis Plan and Data Analysis

2.9

Descriptive statistics with categorical values will be presented as numbers and percentages and continuous values with means with standard deviations (SD) or medians with interquartile ranges (IQR).

The sample size is calculated with regard to the primary outcome, that is the comparison of the prognostic accuracy of the C‐Trend Index and the visual assessment of cEEG at 12 h from ROSC as a reference standard. Firstly, we chose the expected sensitivity and specificity based on the study by Admiraal et al. [12], from which Sandroni et al. [13] calculated sensitivity (63.2%) and specificity (82.1%) for a favorable outcome for EEG with continuous or nearly continuous background with normal voltage, at 12 h from ROSC. Expecting a favorable outcome prevalence of 50%, the accuracy of 72.7% was calculated. The estimated accuracy of the C‐Trend Index used for the calculation was 86.08%, based on our previous work [10]. Accuracy stands for the number and percentage of correctly classified patients, calculated according to a formula (TP + TN)/(TP + TN + FP + FN), where TP and TN stand for the number of true positives and true negatives, respectively, and FP and FN stand for the number of false positives and false negatives, respectively [20]. Calculating the sample size for detecting non‐inferiority with a power of 0.90 and alpha of 0.05, and a non‐inferiority margin of 2%, a sample size of 230 patients is needed. To account for missing or poor‐quality recordings, and drop‐out, we aim to recruit 300 patients.

We will calculate the sensitivity, specificity, negative predictive value (NPV), positive predictive value (PPV), and positive (LR+) and negative (LR−) likelihood ratios with 95% CI for both methods. We will use McNemar's test to compare the two methods.

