The C‐Trend Index values are calculated offline after the recording. The parameter is provided by C‐Trend (Cerenion, Oulu, Finland), a CE‐marked medical device software that utilizes artificial intelligence to capture several power and connectivity features in producing the C‐Trend Index. The parameter ranges from 0 to 100 in values, with higher values referring to higher normal SWA seen during propofol sedation. The parameter is not displayed on the bedside monitor and is not used during the clinical review of the cEEG data. Thus, all clinical and research personnel are blinded to the C‐Trend Index. A running 1‐h average value of the C‐Trend Index is automatically calculated, and for the analysis, the value is picked for each patient from the same time location used in the visual analysis of cEEG.

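### The stated 230 patients for 90% power matches a two-independent-group calculation, but the design is paired; under the stated accuracies the error is conservative and the figure needs restating

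*Protocol article*

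**What the plan says.** The section on statistical analysis takes the visual reading's sensitivity and specificity from the literature ("calculated sensitivity (63.2%) and specificity (82.1%) for a favorable outcome for EEG") and turns them into an accuracy: "Expecting a favorable outcome prevalence of 50%, the accuracy of 72.7% was calculated". The C-Trend Index is assumed to reach 86.08%, from the authors' previous study. The target is "non‐inferiority with a power of 0.90 and alpha of 0.05", with "a non‐inferiority margin of 2" percentage points, and the result is that "a sample size of 230 patients is needed". Recruitment is set at 300 to allow for unusable recordings and drop-out. No formula, sidedness or discordance between the methods is given.

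The Data Extraction section has every recording read visually, and for the C-Trend Index "the value is picked for each patient from the same time location used in the visual analysis of cEEG". The statistical section then names McNemar's test for comparing the two methods.

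**The concern.** Each patient contributes one C-Trend prediction and one visual prediction, both judged against the same 6-month outcome. The precision of the accuracy difference therefore depends on the share of patients on whom exactly one method is correct (the discordance). A calculation for this design needs that share as an input, and none appears. If 230 came from a formula for two separate groups, the stated size and the stated 90% power belong to a different study. The relation between sample size, discordance and true advantage, on which the conclusion depends, is then not visible to the reader.

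**Working it through.** **Inputs** (all from the statistical analysis section unless marked)

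- Visual accuracy p1 = 0.5 × 63.2% + 0.5 × 82.1% = 72.65%, printed as 72.7%.
- C-Trend accuracy p2 = 86.08%. Difference d = 0.8608 − 0.7265 = 0.1343.
- Margin m = 0.02; power 0.90 (z = 1.2816); alpha 0.05, taken as one-sided (z = 1.6449). (1.6449 + 1.2816)² = 8.564.
- Discordance ψ: not given. It is bounded below.

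**Step 1. Reproduce the plan's figure.** For two independent groups with unpooled variance:

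n per group = (zα + zβ)² × [p1(1 − p1) + p2(1 − p2)] / (d + m)²

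= 8.564 × (0.1987 + 0.1198) / 0.1543² = 114.57, so 115 per group and **230 in total**.

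With the rounded 72.7% it is 115.24, so 116 per group and 232 in total. At one-sided 0.025 the same formula gives 141 per group and 282 in total, so one-sided 0.05 is the reading that fits.

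**Step 2. Bound the discordance.** Given the two accuracies:

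- Minimum: ψ = d = 13.4% (C-Trend is right whenever the visual reading is).
- Independent errors: ψ = 0.8608 × 0.2735 + 0.7265 × 0.1392 = 33.7%.
- Maximum: ψ = 2 − 0.7265 − 0.8608 = 41.3% (the two are never wrong together).

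**Step 3. Paired calculation with the same inputs.**

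n = (zα + zβ)² × (ψ − d²) / (d + m)², with d² = 0.0180

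Power at 230 = Φ[(d + m) × √(230 / (ψ − d²)) − zα]

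| Discordance ψ | Patients for 90% power | Power with 230 evaluable |
|---|---|---|
| 13.4% (minimum) | 42 | >99.9% |
| 20% | 66 | >99.9% |
| 25% | 84 | 99.9% |
| 30% | 102 | 99.7% |
| 33.7% (independent errors) | 115 | 99.4% |
| 41.3% (maximum) | 142 | 98.1% |

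With independent errors the paired variance equals the two-group sum in Step 1. The need is then 115 patients who each supply both predictions, half of the stated total.

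**Step 4. Could a paired calculation give 230?** Solving for ψ: 230 × 0.1543² / 8.564 + 0.0180 = 0.66. The accuracies allow at most 41.3%, so it could not.

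**Step 5. Dependence on the assumed advantage** (one-sided 0.05, 230 evaluable patients; discordances are my assumptions)

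- d = 10 points, ψ = 40%: 0.12 × √(230 / 0.39) − 1.645 = 1.27, power about 90%.
- d = 5 points, ψ = 25%: 0.07 × √(230 / 0.2475) − 1.645 = 0.49, power about 69%.

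All figures are large-sample approximations.

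**The case against.** The strongest reply is that nothing harmful follows. 230 evaluable patients exceed every paired requirement, the planned comparison is already paired, and this is an observational substudy of patients already in STEPCARE. That stands, and it is why the point is not more serious.

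A second reply is that the source of 230 is inferred. The article names no formula, and the exact match needs the unrounded 72.65%. This also stands, but the conclusion does not rest on the inference: by Step 4, no admissible discordance yields 230 for a paired non-inferiority test. A two-sided McNemar superiority calculation at 90% power would give about 230 at a discordance near 40%, but the article states non-inferiority with a 2% margin.

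Three stronger readings are tempting and are not supported:

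- A reader might infer that the study is underpowered because the formula is wrong. Under the stated accuracies the opposite is true.
- A reader might infer that alpha must be one-sided 2.5% because the article reports 95% confidence intervals. Those intervals belong to each method's own measures ("We will calculate the sensitivity, specificity, negative predictive value (NPV), positive predictive value (PPV" and likelihood ratios), not to the accuracy difference. An alpha of 0.05 read as one-sided is consistent with the stated figure.
- A reader might infer that 230 patients secure at least 98% power whatever happens, or that recruitment could be cut. Both rest wholly on the 13.4-point advantage, which comes from what the Discussion calls a smaller earlier study. The Discussion adds that previous experience with the index is in sedated patients, whereas half of STEPCARE is randomized to minimal sedation. Step 5 shows how quickly the surplus goes.

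**Conclusion.** The concern holds. The stated 230 patients and 90% power are not those of this paired design. With the article's own accuracies, margin and power at one-sided 0.05, the paired need is 42 to 142, and 230 evaluable patients give about 98% power or more. The rounded 72.7% changes the upper figure only to 143. That 230 is the total of two groups of 115 is a strong inference, not a stated fact. The error is conservative if the C-Trend advantage is as large as assumed. Severity is moderate: a figure the study relies on is wrong for the design, but neither the recruitment target nor the paired comparison has to change because of it.

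**What to change.** Replace the sample-size paragraph with a paired non-inferiority calculation that:

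- states the sidedness of alpha and the assumed discordance as a range, for example the full 13.4% to 41.3% that the accuracies allow;
- restates the power at 230 evaluable patients under the stated accuracies (at least 98% at one-sided 0.05);
- adds a short sensitivity table for a smaller C-Trend advantage, for example about 90% at 10 points with 40% discordance and about 69% at 5 points with 25%, with the discordances labelled as assumptions.

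Keep the target of 300: the surplus over the paired requirement is protection against a smaller true advantage. Moving to one-sided 2.5% is optional and not part of this correction. The cost is a few sentences and one small table, with no change to recruitment or data collection.

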**Methods:**

This is a pre‐planned prospective substudy of the randomized controlled Sedation, TEmperature and Pressure after Cardiac Arrest and REsuscitation (STEPCARE) trial. With a factorial design, the STEPCARE trial evaluates the effects of three different interventions (sedation, temperature management, and mean arterial blood pressure) on functional outcomes in adult out‐of‐hospital cardiac arrest (OHCA) patients. We will record continuous EEG (cEEG) starting as early as possible after ICU admission. We will compare the accuracy (the proportion of correct predictions of all predictions) of C‐Trend Index with that of blinded retrospective visual analysis of cEEG at 12 h after return of spontaneous circulation in predicting favorable functional outcome (modified Rankin Scale 0–3) 6 months after cardiac arrest. We aim to recruit 300 patients to show noninferiority in prognostic accuracy of the C‐Trend Index compared with the visual analysis of cEEG, using a 2% limit for noninferiority. Furthermore, we will assess whether the therapeutic intervention related to sedation, carried out as a part of the STEPCARE trial modifies the performance of the EEG‐based predictors.

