### Primary Study Question

2.4

Is the accuracy of the C‐Trend Index non‐inferior to the blinded retrospective visual analysis of cEEG in predicting favorable outcomes of cardiac arrest patients at 12 h after ROSC?

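### The only comparative test named, McNemar's, ignores the 2-point margin, so a non-significant result leaves the primary non-inferiority question open

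*Protocol article*

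**What the plan says.** The Primary Study Question (section 2.4) is one of non-inferiority: "Is the accuracy of the C‐Trend Index non‐inferior to the blinded retrospective visual analysis of cEEG". The time point it sets is 12 h after ROSC. The hypothesis at the end of Background and Significance is of the same kind, and the abstract fixes the margin, "using a 2% limit for noninferiority".

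Section 2.9, which is headed as the statistical analysis plan, sizes the study on that margin "with a power of 0.90 and alpha of 0.05". For visual cEEG it states "Expecting a favorable outcome prevalence of 50%, the accuracy of 72.7% was calculated". The C-Trend accuracy "used for the calculation was 86.08%, based on our previous work". The result is "a sample size of 230 patients is needed", and 300 are to be recruited.

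The analysis text then lists sensitivity, specificity, predictive values and likelihood ratios for each method with 95% intervals, and closes with "We will use McNemar's test to compare the two methods". The margin is not mentioned again. The Discussion describes the sample size as one for detecting a difference in accuracy of 10% or more, which is the language of a difference test.

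**The concern.** Both methods classify the same patients, so the data are paired. Let b be the number of patients whom only C-Trend classifies correctly and c the number whom only visual analysis does. McNemar's test asks whether b and c have equal expectation. Non-inferiority asks whether the difference in accuracy, (b - c)/n, can be shown to exceed -2 points. These are different hypotheses, and the margin that sized the study plays no part in the test named to analyse it.

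At stake is the main conclusion of the paper. If McNemar's test is not significant, the text as written gives no rule for deciding non-inferiority. The tempting substitute, taking no significant difference as non-inferior, has no controlled error rate. If C-Trend has a moderate true advantage, the test also asks for more than the primary question does.

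**Working it through.** **1. The plan's sample size.** Inputs from section 2.9: sensitivity 63.2%, specificity 82.1%, prevalence 50%, C-Trend accuracy 0.8608, margin 0.02, power 0.90, alpha 0.05.

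Visual accuracy = 0.5 × 0.632 + 0.5 × 0.821 = 0.7265 (72.7% when rounded).

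For two independent groups, n per group = [p_v(1 - p_v) + p_c(1 - p_c)] × (z_alpha + z_power)² / (p_c - p_v + 0.02)².

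With one-sided 0.05: (0.1987 + 0.1198) × 8.564 / 0.1543² = 114.6, so 115 per group and 230 in total. The rounded 0.727 gives 116 and 232. With one-sided 0.025 the total is 282 to 284. The stated 230 therefore corresponds to one-sided 0.05, although the text does not give the sidedness.

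**2. One p-value, two answers.** Take n = 230 and 60 discordant patients. SE = √{[60/230 - (12/230)²]/230} = 0.0335, and 1.96 × SE = 6.6 points.

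| b (C-Trend only correct) | c (visual only correct) | Difference | 95% Wald interval | McNemar p (chi-square; exact) | Non-inferior at -2? |
|---|---|---|---|---|---|
| 24 | 36 | -5.2 | -11.8 to +1.3 | 0.12; 0.155 | Not shown |
| 36 | 24 | +5.2 | -1.3 to +11.8 | 0.12; 0.155 | Shown |

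**3. Behaviour over repeated trials.** The discordant proportion ψ = (b + c)/n is not in the document and is assumed. The table uses n = 230, ψ = 0.30 and 200,000 simulated tables per row. Ranges run over the chi-square and exact forms of McNemar's test at two-sided 0.05. The margin rule requires the lower Wald limit to exceed -2 points.

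| True difference (C-Trend minus visual) | McNemar non-significant | McNemar significant for C-Trend | Margin rule, 95% interval | Margin rule, 90% interval |
|---|---|---|---|---|
| -5 points | 72–76% | below 0.1% | 0.3% | 0.7% |
| -2 points (at the margin) | 92–93% | about 0.5% | 2.6% | 5.0% |
| +5 points | 72–75% | 25–28% | 50% | 62% |
| +13.4 points (the plan's assumption) | 3–4% | 96–97% | 99% | above 99% |

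With ψ from 0.15 to 0.336, McNemar's test is non-significant in 49 to 78% of trials at -5 points.

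**4. The plan's own design point.** The difference is 0.8608 - 0.727 = 0.1338. The discordance can lie anywhere from 0.134 (C-Trend is right wherever visual analysis is) to 0.273 + 0.1392 = 0.412. If the methods err independently, it is 0.727 × 0.1392 + 0.8608 × 0.273 = 0.336.

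McNemar power ≈ Φ{[0.1338√230 - 1.96√ψ] / √(ψ - 0.1338²)}.

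Margin-rule power ≈ Φ{0.1538 / √[(ψ - 0.1338²)/230] - z_alpha}.

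| ψ | McNemar | Margin rule, one-sided 0.05 | Margin rule, one-sided 0.025 | N for 90% power (0.05; 0.025) |
|---|---|---|---|---|
| 0.20 | 99.7% | above 99.9% | above 99.9% | 66; 81 |
| 0.336 | 94% | 99% | 98.5% | 116; 142 |
| 0.412 | 89% | 98% | 96% | 143; 176 |

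At ψ = 0.412 simulation gives 87% (exact) to 89% (chi-square) for McNemar's test.

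**The case against.** A reader might infer that McNemar's test cannot answer the non-inferiority question at all. That goes too far. A significant result in favour of C-Trend shows superiority, which implies non-inferiority at any margin, and under the plan's own accuracies this is the likely outcome. The losses at -5 and +5 points arise away from the design assumption. This part of the objection stands and limits the point to the non-significant case. It does not remove it, because the 13.4-point advantage rests on what the Discussion itself calls a smaller previous study, and the margin matters most when the true advantage is moderate or absent.

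A reader might also infer that the investigators intend to take p above 0.05 as proof of non-inferiority. The document nowhere says so. The 72 to 76% figure is the cost of that reading if someone adopts it, not the error rate of a stated rule.

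Finally, a condensed article may leave an interval for the difference and a decision rule to a full analysis plan or to the Supporting Information, neither of which is shown. Their absence is given no weight here. What counts is that a section headed as the statistical analysis plan names a specific test, and that test does not match the stated hypothesis.

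**Conclusion.** The point holds in a limited form. The plan poses a non-inferiority question with a 2-point margin and names for it only a test of equality that does not use the margin. If McNemar's test significantly favours C-Trend, the question is answered by implication, with about 88 to 99% power at +13.4 points and 230 pairs. If it is not significant, the named analysis leaves the question open: the same p-value fits both a shown and an unshown non-inferiority, and half or more of the trials in which C-Trend is truly 5 points better could show non-inferiority by the margin (50% or 62%), against 25 to 28% by McNemar's test.

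The figures at 5 points assume 230 analysable pairs and 30% discordance, which the document does not give. The mismatch between test and hypothesis depends on neither assumption.

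**What to change.** Replace the McNemar sentence in section 2.9 with wording such as: The primary analysis is the paired difference in accuracy (C-Trend minus visual analysis) with a confidence interval for paired proportions (for example Tango's score or Newcombe's paired method). Non-inferiority is concluded if the lower limit is above -2 percentage points. If it is, superiority is then tested with McNemar's test. A non-significant McNemar result is not evidence of non-inferiority.

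State the level explicitly. A two-sided 90% interval matches the one-sided 0.05 that reproduces 230. A two-sided 95% interval is stricter than the sizing and should be disclosed as such. It still has at least about 96% power with 230 paired patients over the whole possible range of discordance, given the plan's accuracies. The superiority step is optional.

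The cost is a change of wording and a few lines of code, with no new data and no more patients. Section 2.8 has the blinded cEEG analysis done only after the last participant's recording is finished, so the rule can be fixed before those readings exist.

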## Results

3

The plan for presentation of the results is shown in the Supporting Information.

## Discussion

4

We present the rationale and design of a prospective observational substudy of the international cardiac arrest 2 × 2 × 2 platform trial, STEPCARE, which includes adult patients with out‐of‐hospital cardiac arrest of aetiologies not limited to cardiac causes. We will analyse the predictive accuracy of the C‐Trend Index, a measure of the EEG SWA, and compare it with the gold standard, visual analysis of cEEG by investigators blinded to clinical data, in detecting favorable functional outcomes 6 months after OHCA. The C‐Trend Index is a dynamic numerical index provided as a commercially available medical device software. Based on a previous smaller study, accuracy non‐inferior to that of the gold standard is expected in the early phase after ROSC [10]. If this is confirmed, the dynamic numerical nature of the C‐Trend Index may become useful in the clinical care of OHCA patients, as the visual analysis of cEEG depends on specialized expertise in interpreting patterns. A numerical dynamic measure could be feasible for timely bedside interpretation by ICU personnel. Also, the monitoring setup with the frontal electrode and wireless recording device is rapid and easy to apply.

In this study we focus on predicting favorable functional outcome at an early phase after ROSC. The rationale is to provide early information to the patient's family and caregivers and to identify patients with potential for recovery despite eventual slow awakening or unstable clinical course. Furthermore, methods providing prognostic information early may be helpful in certain clinical decisions, such as the timing of for example, cardiac surgery and limiting the duration of sedation.

In the STEPCARE trial, 50% of the patients are randomized to minimal sedation, which allows a proportion of patients with good functional outcomes to wake up early, in some cases even before 12 h post‐arrest. Thus, some patients may not be included in the current study. However, we expect that most patients in the minimal sedation group and all patients in the deep sedation group will be unconscious at 12 h after ROSC. Further, awake patients obeying commands usually have a good functional outcome and thus do not require neuroprognostication. Although multimodal prognostication occurs in a later phase, an early prognostication may provide valuable information, especially for avoiding inadequate withdrawal of care in the future and encouraging continued care in patients with late awakening. As previous knowledge on the performance of the C‐Trend Index in outcome prediction is obtained from patients under sedation [10, 11], assessing the performance of the C‐Trend Index in patients allocated to minimal sedation is also important.

The strengths of this study include the prospective multicenter design with a blinded analysis of the cEEG, a comparison of the C‐Trend Index with a gold standard, and a large patient population with an a priori calculation of the sample size needed to detect at least a 10% difference in accuracy.

The limited number of participating centres in the STEPCARE trial, due to the special equipment required for cEEG recording, may influence the generalizability of the results.

In conclusion, we will compare the predictive accuracy of the C‐Trend numerical index based on EEG SWA with visual assessment of cEEG in predicting favorable functional outcome 6 months after OHCA. We will also assess the effect of the sedation intervention on the predictive accuracy of the C‐Trend Index. If the C‐Trend Index is shown to be non‐inferior in predicting favorable functional outcome, it may provide a valuable information for decision making for ICU clinical staff at an early phase in a dynamic numerical form.

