Here, we present the design and rationale behind the PROPEA STEPCARE, which will compare the ability of the C‐Trend Index to predict favorable functional outcomes at 6 months after cardiac arrest with the gold standard, visual analysis of EEG.

Previous studies indicate that improvement of the C‐Trend‐Index beyond a certain cutoff value or improvement of cEEG pattern to a nearly continuous normal‐voltage background at an early time point after cardiac arrest predicts favorable outcome [10, 11, 12, 13].

Our primary objective is to compare the early predictive accuracy of C‐Trend Index cutoff value 20 with blinded retrospective visual analysis of cEEG in predicting favorable functional outcome at 6 months after cardiac arrest. Furthermore, we will assess the effect of the depth of sedation on the predictive ability of cEEG and C‐Trend Index. Comparing minimal sedation with deep sedation is one of the three interventions carried out as part of the STEPCARE trial [14]. The effect of sedation on the predictive ability of cEEG has been identified as a knowledge gap in the recent international consensus recommendation [4].

We hypothesize that the accuracy of the C‐Trend Index is non‐inferior in predicting favorable outcomes at 12 h after return of spontaneous circulation (ROSC) compared to a retrospective visual analysis of cEEG, blinded to the studied therapeutic intervention and outcome, and that the accuracy will not be impaired by the sedation intervention.

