### Secondary Study Question

2.5

Is the accuracy of C‐Trend Index and visual analysis of cEEG in predicting favorable outcome affected by the sedation intervention of the STEPCARE trial?

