### Management and Study Procedures

2.7

The management in the ICU is according to the STEPCARE trial protocol [14, 16, 17, 18]. A cEEG recording on randomized patients will be initiated as soon as possible after admission to the ICU and continued at least 24 h from ROSC or until the patient awakens to obey verbal commands, whichever comes first. The recording is carried out with a disposable self‐adhesive BrainStatus electrode (Bittium Oyj, Oulu, Finland) attached to the forehead of the patient, including 10 EEG electrodes on positions Fp1, Fp2, Af7, Af8, F7, F8, Sp1, Sp2, T9, and T10, and a wireless BrainStatus recording device (Bittium Oyj, Oulu, Finland). The treating clinical team can decide whether to add more EEG electrodes in addition to the BrainStatus electrode when monitoring cEEG or the performance of intermittent routine EEGs. Electrode placement and initiation of recording are performed according to written instructions.

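### The sedation question compares accuracy between arms after early awakeners have left essentially one arm, so randomisation no longer protects the comparison

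*Protocol article*

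**What the plan says.** The secondary question (Protocol article, section 2.5) is whether the accuracy of the C-Trend Index and of visual analysis is, "in predicting favorable outcome affected by the sedation intervention of the STEPCARE trial". The matching hypothesis in section 1 is "that the accuracy will not be impaired by the sedation intervention".

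Four statements decide who can enter that comparison:

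- Section 2.7: recording runs for at least 24 h from ROSC "or until the patient awakens to obey verbal commands, whichever comes first".
- Section 2.8: the EEG is read in the hour from 11 to 12 h. The fallback hour, within 12 h ± 3 h, is worded for insufficient recording quality. At least 1 h of adequate recording is needed for inclusion.
- Discussion: half of the trial's patients are allocated to the lighter regimen, and the article says that this "allows a proportion of patients with good functional outcomes to wake up early, in some cases even before 12 h post‐arrest". It draws the consequence itself: "Thus, some patients may not be included in the current study".
- Discussion: most minimal-sedation patients, and "all patients in the deep sedation group will be unconscious", are the expectation at 12 h after ROSC.

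The Discussion defends the loss on the ground that awake, obeying patients usually do well and need no prognostication. It does not say what the loss means for the comparison between sedation arms.

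**The concern.** Leaving the analysis by waking happens after randomisation, is brought about by one of the two allocations, and goes with good outcome. A deep-sedation patient who would have woken early under minimal sedation stays in; the counterpart in the minimal-sedation arm drops out. The two analysed groups are then no longer the groups that randomisation made comparable.

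Accuracy is exposed in two ways. It is a prevalence-weighted mean of sensitivity and specificity, so removing good-outcome patients from one arm changes the weights. If early awakeners also have better (or worse) EEGs than other good-outcome patients, sensitivity in that arm changes as well. Either can look like a sedation effect, or offset a real one. Section 1 describes the effect of sedation on EEG prediction as a recognised knowledge gap, so the answer is likely to be read as an effect of sedation.

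**Working it through.** **Inputs from the article**
- Visual EEG, favorable outcome: sensitivity (Se) 0.632, specificity (Sp) 0.821, prevalence 0.50 (section 2.9).
- C-Trend Index, cutoff 20: specificity 95% and sensitivity 83% for unfavorable outcome (section 1). Turned round for favorable outcome, Se = 0.95 and Sp = 0.83.
- 230 evaluable patients (section 2.9) with 1:1 sedation allocation, so about 115 per arm.

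**Assumptions.** The article gives no share of early awakeners. Let f be the share of the minimal-sedation arm excluded for waking, all with favorable outcome; f = 10% and 20% are illustrations. The deep-sedation arm loses nobody. Before exclusion, Se and Sp are the same in both arms, so there is no true sedation effect.

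**The plan's own figure.** Accuracy = 0.5 × 0.632 + 0.5 × 0.821 = 0.7265, which agrees with the stated 72.7%. For C-Trend the split above gives 0.5 × 0.95 + 0.5 × 0.83 = 0.89. The planning value in section 2.9 is 86.08%, so it is checked separately below.

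**Case 1: every awakener would have been a true positive.** Shift = (acc - f)/(1 - f) - acc.
- Visual, f = 10%: (0.7265 - 0.10)/0.90 = 0.6961, shift -3.0 points. f = 20%: 0.5265/0.80 = 0.6581, shift -6.8.
- C-Trend, f = 10%: 0.79/0.90 = 0.8778, shift -1.2. f = 20%: 0.69/0.80 = 0.8625, shift -2.8.
- C-Trend started from 0.8608: 0.7608/0.90 = 0.8453, shift -1.5; 0.6608/0.80 = 0.8260, shift -3.5.

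**Case 2: awakeners would have been classified at average sensitivity.** Only prevalence moves. At f = 10% it becomes (0.50 - 0.10)/0.90 = 0.444.
- Visual: 0.444 × 0.632 + 0.556 × 0.821 = 0.737, shift about +1.0.
- C-Trend: 0.444 × 0.95 + 0.556 × 0.83 = 0.8833, shift -0.7.

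**Does conditioning on outcome cure it?** Not fully. It removes the whole of case 2 but not case 1. There, apparent visual sensitivity at f = 10% is (0.316 - 0.10)/(0.50 - 0.10) = 0.54, against 0.632 in the deep-sedation arm.

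**Precision of the arm comparison.** The 95% half-width is 1.96 × √(2p(1 - p)/115): 11.5 points for visual EEG (p = 0.7265) and 8.9 points for C-Trend (p = 0.8608).

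**The case against.** Much can be said for the plan. The exclusion is acknowledged and justified, and accuracy among patients still unconscious at 12 h under each regimen is a coherent, clinically useful quantity. The article expects most minimal-sedation patients to be unconscious then, so f may be small. Every shift above is smaller than the half-width of the matching interval, and the C-Trend shifts are small in absolute terms. The fallback window might also keep some who wake after about 10 h, if a missing 11 to 12 h recording counts as insufficient quality.

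These points limit the size. They do not restore comparability: the groups still unconscious at 12 h are selected differently in the two arms, and a wide interval does not remove a bias. The argument that awake patients need no prognostication supports the primary target population, not a contrast between arms.

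Stronger readings are tempting, but the text does not support them:
- A reader might infer that McNemar's test is misapplied to the arms. Section 2.9 assigns it only to comparing the two methods, where it fits.
- A reader might fault the absence of a margin for the hypothesis of no impairment, or expect a non-significant difference to be taken as proof of it. The first is detail that a condensed article may leave to the full plan; no such decision rule is stated.
- A large upward shift can be constructed (visual +8.1 points at 10%, from 0.7265/0.90 = 0.8072), but only if every awakener were an EEG false negative. That runs against the article's own account that early EEG recovery goes with favorable outcome.

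**Conclusion.** The point holds for the secondary sedation question only. As described, a raw between-arm difference in accuracy mixes any sedation effect with selection after randomisation. With no true effect and an assumed 10% exclusion, the selection part is -3.0 to about +1.0 points for visual EEG and -1.2 to -0.7 for C-Trend; at 20%, with all awakeners true positives, it is -6.8 and -2.8. These figures rest on an assumed share of awakeners, all with favorable outcome, and on the article's planning values. If few patients wake before about 12 h, the effect is slight.

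A reader might infer that the primary non-inferiority comparison is biased too. It is not affected in this way: both methods are read in the same patients at the same time point, so the loss of awakeners defines the population it applies to and does not unbalance the comparison. Nor can it be said that exclusion will produce an apparent sedation effect; the documents show that it can distort the estimate, in a direction that depends on who leaves.

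**What to change.** For the sedation question, before the EEGs are read:

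1. State that the main target is patients still unconscious with an evaluable EEG at about 12 h.
2. Compare sensitivity and specificity between arms alongside accuracy, and give each arm difference with its 95% CI.
3. Report, by arm, how many patients were excluded for awakening and their 6-month outcome.
4. Add a sensitivity analysis that keeps the awakeners and classifies them both ways, all correct and all incorrect. The resulting range for the minimal-sedation arm is as wide as the awakener share (10 points at 10%), so it is informative only if that share is small. Where a recorded hour before awakening exists, also classify by that hour, noting that it is earlier than 12 h and arises almost only in one arm, so arm and reading time are confounded. Very early awakeners may have no such hour.
5. Attribute an arm difference, or its absence, to sedation only if it holds across these analyses.

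The cost is a little extra analysis and a more cautious secondary conclusion. No further patients are needed, and the primary analysis is unchanged.
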